**Methods/Design:**

Design: Cross-sectional, multicentre study.

Setting: 25 urban health care centres.

Study population: Randomly selected sample of Spanish/Catalan speakers age 16 or above with a medical register in any of the 25 participating primary health care centres. N = 1540.

Unit of study: Basic unit of care, consisting of a general practitioner and a nurse, both of whom caring for the same population (1,500 to 2,000 people per unit).

Instruments of measurement: Data collection will be performed using a survey carried out by health professionals, who will use the clinical registers and the information reported by the patient during the visit to collect the baseline data: illnesses, medication intake, alcohol and psychoactive consumption, and self perception of risk.

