### The situation in Primary Care

In our country, few articles have been published on RTI and their impact in Primary Health care. Most of them, written during the 1990's have consisted of descriptive epidemiological studies on the impact of road traffic injuries on the number of emergency consultations, its prevalence according to age groups and gender and studies on time, place and gravity of the RTI. If summarised, they show that the frequency of RTI is approximately 8 per 1,000 inhabitants [35,36] making up 4.1% of all consultations in a primary health care centre [37]. Of all collision accidents of any kind, those on a public road are the second most frequent, after domestic accidents, road traffic injuries making up between 8.3% and 8.6% of all kinds [37-39].

The most serious RTI happen on the road, and affect male drivers more (approximately 70%), with an average age of 27 ± 3 years [35-37], with a large peak in the group around 20 ± 5 years of age (42.8% of cases) [36]. The impact makes up 1% of the total of patients attended in an emergency centre [40].

Diverse authors warn of the high occurrence of RTI in children (245 per 1,000 inhabitants) [38], and the importance of the use of child protection methods in vehicles. 20.75% of child accidents correspond to the RTI that affect those aged 12 ± 2 years [41,42].

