## Objectives

Main aim: to assess the distribution of the risk factors associated with RTI in a driving population assigned to a group of participating primary health care centres in the city of Barcelona.

Secondary objectives: 1. To study the distribution of RTI risk factors relative to medications, illnesses, alcohol intake and/or consumption of psychoactive substances in the driving population in different groups according to age and gender. 2. To outline the correlation between the number of risk factors related to suffering an RTI and the background of registered collisions, having or not having recieved medical attention. 3. To assess the existing relationship between the self perception level of risk of RTI and the presence of chronic health conditions, medication or consumption of psychoactive substances.

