### Sample size calculation

The calculation was carried out using the population of men and women with a driving license in the Barcelona province from the age 16 and over, according to the 2005 census of drivers made available by the General Traffic Department (DGT). For sample calculation purposes, four age groups proportional to women and men were created. Accepting an alpha risk of 0.05 with a precision of +/- 0.05 percentage units in a bilateral contrast for an estimated proportion of 0.5, a random population sample of 385 subjects was determined for each age group. The total sample size is 1540 subjects (Table 3).

**Table 3 T3:** Sample size according to the estimated distribution in age and gender groups

	16-24 yrs	25-34 yrs	35-64 yrs	Above 74 yrs	Total
Men	214	212	228	317	971
Women	171	173	157	68	569

Total	385	385	385	385	1540

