### Recruitment Process

The study population will be recruited by consecutive sampling. Each collaborating researcher, after verifying the inclusion criteria, will include 16 subjects, two for every age and gender group of those described in the table above. All subjects of 16 years of age or over that consult any collaborating health professionals (nurses or doctors) for any motive, will be invited to participate. They will be informed by the collaborating researcher (patient information leaflet) and asked to take part in the study and in yearly follow-ups via telephone. In case of acceptance, they will read and sign a consent form. Each centre will recruit patients until reaching the number of participants stipulated, taking into account the necessary distribution by age groups and sex. Figure 1 Flow Chart: Algorithm of the study shows the recruitment system and yearly monitoring.

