#### Exclusion criteria

people who do not poses a telephone contact number; those with serious psychiatric problems; those with physical or psychiatric disabilities that impede their participation in the study; those with a terminal illness.

All centres of Barcelona province and the metropolitan area will be invited to participate, and those who voluntarily accept to participate will be included in the study. *To date, at the end of the recruitment period, 25 practices will participate in the study*.

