### Study variables

#### We dispose of two data collection instruments in order to carry out this study

-A survey, which will be carried out by health professionals in a face to face interview. Data will be obtained from the clinical register, and double-checked by the researcher and patient during the visit.

In this survey, the following will be noted: 1. Demographic data: age, gender, civil status, place of origin, level of studies, social class (according to the categories proposed by the Spanish Epidemiology Society). 2. Medication: long-term medication, acute medication (taken in the last 30 days). 3. Chronic health conditions related to higher risk of RTI (Table 3). 4. Alcohol consumption (measured using the AUDIT-C test). 5. Consumption of psychoactive substances (cocaine, ecstasy and others) during the last year, as self-reported by the patient and self-declared dependency level of psychoactive substances in the last month. 6. Estimated level of perception risk, as assessed by the health professional, and rated using a scale from 0 (no risk) to 10 (maximum risk). 7. Driving data: type of driver's license, length of time driver's license held; type of vehicle most usually driven (moped, motorbike, car, others); professional driver (y/n); time spent driving in hours per week; type of road usually used (urban, motorway or others); safety behaviours (use of seatbelts, use of helmet, use of car seats for children and adherence to speed limits). 8. Collision background in the last year (with or without injury); History of medical attention for traffic road injuries in the last year. 9. Self-declared self medicating. 10. Self evaluation of state of health (using the SF-12 test). 11. Self-perception of risk. Individuals will be asked to score their own risk for RTIs, when compared to subjects with their same gender and age, rated in a scale from 0 to 10.

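### A visit made for a traffic injury can itself supply the collision history, which overstates collision frequency and may weaken the association sought in secondary objective 2

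*Protocol article*

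**What the plan says.** Recruitment Process states that "The study population will be recruited by consecutive sampling" and that subjects of the required age "that consult any collaborating health professionals (nurses or doctors) for any motive, will be invited to participate", filling age and sex cells. The Inclusion criteria cover age, language, licence and consent. The Exclusion criteria begin with "people who do not poses a telephone contact number; those with serious psychiatric problems" and go on to disability that prevents participation and terminal illness. Neither list refers to the reason for the visit.

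Secondary objective 2 reads "To outline the correlation between the number of risk factors related to suffering an RTI and the background of registered collisions", whether or not medical care was received. The variable behind it, item 8 of the face-to-face survey under Study variables, is "Collision background in the last year (with or without injury); History of medical attention for traffic road injuries in the last year". None of the eleven items listed for that survey is the reason for the visit or the date of a collision. The later telephone survey does list the date.

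The situation in Primary Care describes traffic injuries as "making up 4.1% of all consultations in a primary health care centre". Difficulties and limitations of the study does not mention selection through attendance. Two other places describe a different kind of sample: the Abstract has a "Randomly selected sample of Spanish/Catalan speakers age 16 or above with a medical register", and Sample size calculation says that "a random population sample of 385 subjects was determined for each age group".

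**The concern.** A patient who attends because of a recent crash has the outcome of objective 2 at the moment of invitation. People who crash and seek care therefore have an extra route into the sample that people who do not crash lack.

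Two things are at stake. The first is any collision proportion reported from the survey, which would be read as describing drivers. The second is the link between number of risk factors and collisions. Chronic illness and medication also generate visits. If attendance rises with risk factors and with collisions, the relation between the two among attenders need not match the relation among drivers.

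**Working it through.** **The plan's own figure.** n = 1.96² × 0.5 × 0.5 / 0.05² = 384.15, rounded up to 385 per age group; 4 × 385 = 1540. This reproduces, and nothing below changes it.

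**Inputs from the article.** Traffic injuries are 4.1% of primary care consultations, about 8 per 1,000 inhabitants, and 1% of patients in an emergency centre (The situation in Primary Care). A survey found 17.8% injured in the last year (Background). Average visits are 5 to 6 a year (Discussion). The relative risk for a chronic condition is 1.33 (Chronic health conditions).

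**Number entering at a traffic visit.** 0.041 × 1540 = 63; 0.010 × 1540 = 15; 0.008 × 1540 = 12.

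**Is 4.1% usable as it stands?** Taking 8 per 1,000 as yearly, visits per injury would be 0.041 × 5 / 0.008 = 25.6 to 0.041 × 6 / 0.008 = 30.8. That is implausibly many, so 4.1% is treated as an upper bound and 0.8% as a low value.

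**Collision frequency.** Let s be the share recruited at a traffic visit, all counted as having a last-year collision, and p the true frequency in everyone else. Observed frequency = s + (1 − s)p, so the excess is s(1 − p). The range for p, 2% to 17.8%, is an assumption.

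| p | excess, s = 0.8% | excess, s = 4.1% | 95% half-width, N = 1540 |
|---|---|---|---|
| 2% | 0.78 points | 4.02 points | 0.70 points |
| 5% | 0.76 | 3.89 | 1.09 |
| 10% | 0.72 | 3.69 | 1.50 |
| 17.8% | 0.66 | 3.37 | 1.91 |

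The half-width is 1.96 × √(p(1 − p)/1540), as for a simple random sample. At s = 0.8% the bias is about the size of sampling error or smaller. At s = 4.1% it is well above it throughout.

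**Association in objective 2.** Let S be the chance of capture in each combination of risk factor (first index) and collision (second index). The observed odds ratio is the true one times (S11 × S00)/(S10 × S01).

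- Capture depends on collision only: the factors cancel. With 30% exposed, 5% collisions in the unexposed and an odds ratio of 1.33, doubling capture after a collision moves the overall frequency from 5.5% to 10.4%. The odds ratio stays at 1.33.
- Capture proportional to visits, with 5.5 baseline visits, m extra for risk factors and k extra after a collision: factor = (5.5 + m + k) × 5.5 / [(5.5 + m)(5.5 + k)]. For m = 2, k = 1 it is 46.75/48.75 = 0.96; for m = 6, k = 3 it is 79.75/97.75 = 0.82. Using 1.33 as an illustrative odds ratio gives 1.28 and 1.09.
- Stronger assumption: half the drivers exposed, 8 visits if exposed and 3 if not (mean 5.5). Factor = (8 + k) × 3 / [(3 + k) × 8] = 0.84, 0.75 and 0.69 for k = 1, 2 and 3. The 1.33 becomes 1.12, 1.00 and 0.91.

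The values of m, k and the 8-and-3 split are assumptions; the article gives none of them. If a crash multiplied visits by the same ratio in ill and healthy people, the factor would be 1.

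**The case against.** The strongest reply is that objective 2 concerns an association and that no stated objective estimates collision frequency. Outcome-dependent sampling leaves an odds ratio intact, as in a case-control study. Study population also defines the target as drivers who have been attended, so broad recruitment is partly by design. This stands as far as it goes: a reader might infer that extra crash visits inflate objective 2, and they do not do so on their own. It does not dispose of joint selection on collisions and risk factors. It also presumes an odds ratio, whereas Objectives speaks of a correlation and Statistical analysis assigns logistic regression to risk perception. A correlation coefficient or a risk difference can shift with outcome frequency.

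A reader might also infer that the association could be hidden or reversed. The 8-and-3 illustration with k = 3 does fall below 1, but only under visit counts that the article does not supply. There is an opposing force as well. Acute medication in the previous 30 days is recorded, and analgesics, anti-inflammatories and muscle relaxants are among the drugs the article names as affecting driving. A crash may therefore create the risk factor, and the size of this upward push cannot be computed.

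The inputs are weak, and that too stands. The 4.1% comes from mostly 1990s studies and fits poorly with the other figures. The 0.8% is injuries per inhabitant, not collisions of any kind among drivers, so setting an observed 4.9% (0.041 + 0.959 × 0.008) against 0.8% compares unlike quantities. Quota recruitment makes a uniform share doubtful.

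The article condenses the survey, and the data collection booklet is not shown; it may record the reason for the visit. If so, only the analysis rule is needed.

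Finally, dropping crash visits might itself look like selection on the outcome. It is not in the harmful sense: capture then depends only on visits made for other reasons, and people with earlier collisions still enter through those.

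**Conclusion.** The concern holds in a limited form. As written, recruitment lets the index visit supply the outcome, and the listed limitations do not say so. Collision frequency is overstated relative to drivers at large by roughly 0.7 to 4 points. This rests on 0.8% to 4.1% of recruiting visits being for a traffic injury, on a true frequency of 2% to 17.8%, and on each such visit being counted as a last-year collision. The upper end is a ceiling, not a best estimate.

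For objective 2, distortion requires attendance to rise with both collisions and risk factors. That is plausible and would most likely pull the association toward the null. The size depends wholly on assumed visit counts, and the documents do not establish reversal. The sample size is unaffected.

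**What to change.** 1. Add one survey item, unless the booklet already has it: is today's visit caused by a traffic collision or its after-effects (yes/no)?
2. Analyse objective 2 and any collision proportion without subjects who answer yes, or invite such patients only at a visit made for another reason. Report the all-subjects analysis alongside as a sensitivity analysis.
3. List attendance-based selection among the limitations, and bring the Abstract and Sample size calculation, which describe a random sample, into line with Recruitment Process.

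The cost is one tick box and one analysis rule. At most about 4% of subjects (63 of 1540) leave those analyses, or none if they are invited at another visit or replaced within the cell. There will also be fewer medically attended collisions to analyse.

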**Figure 1 F1:**
[figure not shown]
**Flow Chart: Algorithm of the study**.

### Selection criteria

#### Inclusion criteria

aged 16 or above; sufficient understanding and knowledge of Catalan or Spanish; possession of valid driving or motorbike license; subject's agreement to participate in the study and in yearly follow ups via telephone through a signed consent form.

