### Study population

Drivers aged 16 or above who have been attended and who have a clinical register at the participating primary health care centres.

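### The aim and study population are worded as drivers, but eligibility rests on holding a licence, so the planned driver prevalences are prevalences among licence holders

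*Protocol article*

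**What the plan says.** Under Objectives, the main aim is "to assess the distribution of the risk factors associated with RTI in a driving population". The Study population section begins "Drivers aged 16 or above who have been attended". Inclusion criteria put this into practice through "possession of valid driving or motorbike license", together with age, language and consent. Exclusion criteria cover lack of a telephone, serious psychiatric problems, disability that prevents participation, and terminal illness. Neither list mentions current driving.

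The Sample size calculation uses the same licence-based frame: "the population of men and women with a driving license in the Barcelona province from the age 16 and over". It sets 385 subjects in each of four age groups, 1540 in all; Table 3 labels the oldest group as above 74 years.

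The baseline survey (Study variables) records "time spent driving in hours per week", the vehicle most often driven, the road type, and collisions in the last year. The Statistical analysis section gives these driving data no role in defining who is analysed. It says in general terms that confounding will be examined. The limitations section does not mention licence holders who do not drive.

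**The concern.** A licence shows permission to drive, not driving. The risk factors under study were chosen because they are thought to impair driving, and the advice for the highest drug category in Table 2 is against driving. It is therefore plausible that non-driving licence holders carry more of these factors than active drivers do. If so, counting them as drivers raises the estimated prevalence of illness and medication among drivers, which is what the main aim and secondary objective 1 are meant to deliver.

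Secondary objective 2 relates the number of risk factors to past collisions. Subjects with many risk factors and little or no driving would tend to weaken that association.

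**Working it through.** **The plan's own figure.** For one proportion, n = 1.96² × p(1 − p) / d². With p = 0.5 and d = 0.05 (Sample size calculation), n = 384.15, rounded up to 385; 4 × 385 = 1540. Both stated figures reproduce, and nothing here disputes them.

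**Prevalence.** Let f be the share of a stratum that does not drive. Bias = f × (prevalence in non-drivers − prevalence in drivers). Neither term is in the documents. The gap is assumed to be 20 points and f is varied from 5% to 40%. The half-width for active drivers alone is 1.96 × √(0.25 / (385 × (1 − f))).

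| f (assumed) | Active drivers of 385 | Half-width, active drivers (points) | Overstatement if all are counted as drivers (points) |
|---|---|---|---|
| 5% | 366 | 5.12 | 1 |
| 10% | 347 | 5.26 | 2 |
| 20% | 308 | 5.58 | 4 |
| 30% | 270 | 5.97 | 6 |
| 40% | 231 | 6.45 | 8 |

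The overstatement exceeds the planned 5 points once f is above 0.05 / 0.20 = 25%. With a 10-point gap it halves, to between 0.5 and 4 points. With no gap it is zero.

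If only the oldest stratum is affected, an unweighted estimate over all 1540 moves by a quarter of this: 0.25 × 4 = 1 point at f = 20% and 0.25 × 8 = 2 points at f = 40%. The half-width for 1540 is 1.96 × √(0.25 / 1540) = 2.5 points.

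**Collisions.** Assume an 8% annual collision risk among drivers, no true effect of the risk factor, and zero collision risk in non-drivers.

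- Non-driving 10% without the factor and 30% with it: risks 0.08 × 0.90 = 0.072 and 0.08 × 0.70 = 0.056; OR = (0.056 / 0.944) / (0.072 / 0.928) = 0.76.
- Non-driving 5% and 15%: risks 0.076 and 0.068; OR = 0.89.

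The zero risk is an extreme setting, because the baseline collision item is not limited to collisions while driving. If non-drivers have half the drivers' risk (0.04, also assumed):

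- 10% and 30%: risks 0.072 + 0.10 × 0.04 = 0.076 and 0.056 + 0.30 × 0.04 = 0.068; OR = 0.89.
- 5% and 15%: risks 0.078 and 0.074; OR = 0.94.

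If non-driving is equally common with and without the factor, the risk ratio does not change.

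**The case against.** The strongest reply is that the plan uses one working definition throughout. The sample size frame is licence holders, the inclusion criterion matches it, and the licence must be valid. On that reading, driver simply means licensed driver. This stands for the sample size, which is unaffected. It does not settle the wording of the aim and study population, which a reader will take to mean people who drive.

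A second reply is that analysis populations and covariates are often left to a statistical analysis plan, and that the general statement on confounding leaves room for driving hours. That is fair, and the absence of a covariate list is not the point here. The point is that target population and eligibility, both stated in the article, do not match.

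Third, the documents do not say that people stop driving because of the conditions studied, nor how often. This also stands: direction is plausible, size is assumed, and at 5% to 10% non-driving the overstatement is only 1 to 2 points.

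A reader might infer more: that non-drivers cannot have a collision, so objective 2 must be pulled to or below the null, and that it should be analysed only in subjects with more than 0 driving hours. The documents do not support this. The baseline item counts any collision in the last year, and the Background itself names pedestrians over 65 as a high-risk group. Collisions cover the past year while hours are asked at the visit, so someone who crashed and then stopped driving would be removed along with the collision. Adjustment for hours has a limit too: it may block part of any effect of illness that works through driving less.

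**Conclusion.** The mismatch is real and lies in the article's own text: the main aim and secondary objective 1 would yield prevalences among licence holders under a label of drivers. On an assumed 20-point gap, the overstatement within a stratum is 1 to 8 points for 5% to 40% non-driving. It matters against the planned 5 points mainly if more than about a quarter of a stratum do not drive. The oldest group is where this is most plausible; the documents give no figure for it or for the younger groups.

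For the collision objective the conclusion is weaker. Differential non-driving could dilute the association, but ORs of 0.76 and 0.89 under no true effect are extreme illustrations. The article also disclaims causal assessment. What is justified there is transparent reporting with and without driving exposure, not a change of the analysed population.

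**What to change.** **Main aim and secondary objective 1.** Define an active driver from the weekly hours and usual vehicle already recorded, and state how occasional drivers who report 0 hours per week are classified. Report prevalences for active drivers beside those for all licence holders, by age group and sex. If the sponsor prefers to keep licence holders as the target, reword the aim, study population and table labels accordingly.

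**Secondary objective 2.** Keep all licence holders. Present the association between number of risk factors and collisions both without and with adjustment for weekly driving hours. Show any restriction to active drivers only as a sensitivity analysis, with a note that hours are asked after the year in which collisions are counted.

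**Cost.** A short addition to the analysis section and no new data. Precision for active drivers falls somewhat, chiefly in the oldest group: a half-width of about 5.6 instead of 5.0 points if 20% do not drive. Holding 385 active drivers in a stratum at that share would need 385 / 0.80 = 481.25, so 482 enrolled; this is optional and not needed for the reporting change.
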